### Follow-Up Protocol

All participants will be followed up 12 months after discharge via telephone by a trained physician using a structured interview. In cases of suspected hernia, patients will be invited for outpatient clinical examination and ultrasound or CT imaging to confirm the diagnosis.

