**Methods:**

This national, prospective, multicentre, observational cohort study will include adult patients undergoing emergency abdominal surgery for specific indications such as acute appendicitis, cholecystitis, incarcerated hernias, gastrointestinal perforation, or bowel obstruction. The study period extends from 1 June 2025 to 31 December 2026, with recruitment completed by the end of 2025 and follow-up completed by the end of 2026. Data on demographics, comorbidities, surgical techniques, postoperative management, and complication rates will be collected. The primary endpoints are incisional hernia, port-site hernia, and parastomal hernia. Secondary endpoints include surgical site infections (SSI) and burst abdomen. Follow-up will be conducted via structured telephone interviews and clinical or imaging confirmation. Based on power calculations for primary and secondary outcomes, the study will include 500 patients, providing adequate statistical strength while maintaining feasibility across participating centres.

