## Methods and Design

### Study Design and Registration

The PROPHECY trial is a prospective, multicentre, observational cohort study conducted across multiple surgical centres in Poland. The study will run from June 2025 to December 2026, with follow-up and final data analysis planned for early 2027. It is coordinated by the Department of Surgical Sciences and the Laboratory of Medical Genetics of the Medical College, Jan Kochanowski University in Kielce, Poland. Ethical approval was granted by the Institutional Bioethics Committee (Decision No. 5/2025), and the study is registered at ClinicalTrials.gov (NCT06815822). This protocol is published prior to patient enrolment in order to enhance methodological transparency, facilitate reproducibility, and reduce the risk of selective reporting.

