### Study Timeline

• Centre enrolment: May 2025• Patient recruitment: 1 June 2025–31 December 2025• Follow-up period: 1 January 2026–31 December 2026• Data analysis: January 2027• Expected publication: February/March 2027

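### The stated recruitment, follow-up and analysis dates cannot all be met with an interview 12 months after discharge for every participant

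*Protocol article*

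**What the plan says.** Four places in the protocol article bear on this.

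- Follow-Up Protocol: "All participants will be followed up 12 months after discharge via telephone by a trained physician using a structured interview". Where a hernia is suspected, "patients will be invited for outpatient clinical examination and ultrasound or CT imaging to confirm the diagnosis". No time is allotted to that second step.
- Study Timeline: "Patient recruitment: 1 June 2025–31 December 2025", then "Follow-up period: 1 January 2026–31 December 2026". Data analysis is set for January 2027 and publication for February or March 2027.
- Abstract, Methods: the study period ends on 31 December 2026, "with recruitment completed by the end of 2025 and follow-up completed by the end of 2026". This agrees with the Study Timeline.
- Study Design and Registration: the study runs to December 2026, but "with follow-up and final data analysis planned for early 2027".

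The article gives no length of stay and no date for database lock.

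**The concern.** The follow-up clock starts at discharge, but the calendar allows exactly 12 months after the last recruitment day. Any patient still in hospital at the end of 2025 is therefore due in 2027. A centre reading the article cannot tell whether to make that call early, on time or not at all. The confirmatory step has no room either: a call made on the last day of follow-up leaves no days for examination and imaging.

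All three primary endpoints (incisional, port-site and parastomal hernia) rest on this single contact and its confirmation. An early call shortens the time at risk, a call not made loses the outcome, and a suspected hernia not yet examined has no settled status when the analysis starts.

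**Working it through.** **Inputs from the article.** Recruitment 1 June to 31 December 2025; follow-up close 31 December 2026; analysis January 2027; interview 12 months after discharge; N = 500; 255 patients for 5% precision on hernia incidence (Sample Size Justification).

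**Assumptions, not in the article.** Uniform accrual; mean stay 3 to 15 days; 4 weeks (28 days) from a suspicious call to completed examination and imaging.

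**1. Reproducing the stated close.** 31 December 2025 + 12 months = 31 December 2026. The close is reproduced if the 12 months run from recruitment or surgery. Counted from discharge, it holds only if no recruited patient is in hospital after 31 December 2025:

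| Discharge | Interview due | Days after close |
|---|---|---|
| 31 December 2025 | 31 December 2026 | 0 |
| 1 January 2026 | 1 January 2027 | 1 |
| 7 January 2026 | 7 January 2027 | 7 |
| 31 January 2026 | 31 January 2027 | 31 |

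**2. Patients due after the close.** The window is 214 days, so accrual is 500/214 = 2.34 per day. The expected number in hospital at year-end is accrual × mean stay:

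| Assumed mean stay (days) | Patients | Share of 500 |
|---|---|---|
| 3 | 7 | 1.4% |
| 5 | 12 | 2.3% |
| 7 | 16 | 3.3% |
| 10 | 23 | 4.7% |
| 15 | 35 | 7.0% |

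**3. Who they are.** Patients in hospital on a fixed date over-represent long stays. In a simulation with lognormal stays (assumed log-SD 0.8), about 79% of them stay longer than the overall median and about 55% fall in the top quarter. About 21% have a stay at or below the median and are caught only because they were operated on in the last days of December.

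**4. Suspected hernias without time for confirmation.** The incidence behind n = 255 solves 1.96² × p(1 − p)/0.05² = 255, which gives p ≈ 0.21. Check: 3.84 × 0.21 × 0.79/0.0025 ≈ 255. This incidence stands in for the share of interviews that raise suspicion.

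- Calls falling in the last 28 days of follow-up: 28/214 × 500 ≈ 65 patients; × 0.21 ≈ 14.
- Adding those due after the close, mean stay 5 days: (28 + 5)/214 × 500 ≈ 77; × 0.21 ≈ 16.
- The same with mean stay 15 days: (28 + 15)/214 × 500 ≈ 100; × 0.21 ≈ 21.

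So about 14 to 21 of roughly 105 expected hernias (0.21 × 500) are exposed. The lower figure counts late calls only; the upper ones also include patients from step 2, so the two counts should not be added.

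**5. Size of the bias.** Suppose the k late patients are lost entirely and have double the risk (42% against 21%; both the doubling and the complete loss are assumed). Only 21% would then be observed, while true incidence is [0.21(500 − k) + 0.42k]/500, an understatement of 0.21k/500.

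- k = 12: 0.2150, understated by 0.5 percentage points.
- k = 23: 0.2197, understated by 1.0 percentage point.

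The planned precision is 5 percentage points.

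**The case against.** The strongest reply is that Study Design and Registration already places follow-up in early 2027, so late calls may be intended, and that call windows and confirmation deadlines belong in the full protocol. Part of this stands: a missing call window is no fault in an article, and it is wrong to treat the December 2026 close as the only date given. But the early-2027 statement contradicts the Abstract and the Study Timeline, and its own sentence also ends the study in December 2026. Calls in January 2027 would also coincide with the scheduled analysis. The article states its dates, and they disagree.

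The second reply is that little is lost. A patient discharged on 7 January 2026 and called on 31 December 2026 is one week short of 12 months, and few hernias would be missed. That also stands, and it limits the severity.

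Three stronger readings may tempt a reader, and the article does not support them.

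- That the affected patients are the long-stay, high-risk ones. No length of stay, and no risk by stay, is given. The group also includes short-stay patients operated on at the very end of December, and long-stay patients recruited earlier are unaffected. Over-representation of long stays is as far as one can go.
- That 15 to 20% of the cohort (77 to 100 patients) is compromised, beyond the 10% dropout allowance. Examination and imaging follow only a suspicious interview; a patient with a negative interview in December 2026 has complete data. The comparable figure is the 1 to 7% due after the close, which is below 10%.
- That suspected hernias will be unconfirmed at database lock. No lock date is stated, and nothing requires confirmation to end by 31 December 2026. The risk comes from starting the analysis in January 2027.

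**Conclusion.** The point holds as an internal inconsistency of minor to moderate weight. The calendar in the Abstract and Study Timeline cannot deliver the assessment that the Follow-Up Protocol promises to every participant, and Study Design and Registration adds a conflicting date instead of settling the matter.

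The contradiction is a matter of dates and needs no assumption beyond at least one recruited patient being in hospital after 31 December 2025. The sizes do rest on assumptions: about 1 to 7% of patients due late (uniform accrual, mean stay 3 to 15 days) and about 14 to 21 suspected hernias without time for confirmation (4-week work-up, suspicion rate equal to the implied 21% incidence; a higher suspicion rate would raise this). Downward bias is plausible but small, about 0.5 to 1 percentage point under deliberately unfavourable assumptions for 12 to 23 patients.

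**What to change.** Reconcile the Abstract, Study Design and Registration, Study Timeline and Follow-Up Protocol in one of two ways.

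- **Extend follow-up (preferred).** Keep 12 months after discharge for every patient. Define the close as the last discharge plus 12 months, plus the call window, plus a confirmation period, and start the analysis after that. Build the date from these parts, because a fixed date can fall short: with a call window of up to 2 months and a 4-week work-up, a patient discharged on 15 January 2026 could be called until 15 March 2027 and confirmed by 12 April 2027. The cost is a delay of a few months to analysis and publication, with no extra patients or procedures.
- **End recruitment earlier.** Stop early enough that the last call and its confirmation fall within 2026. With a 4-week work-up the last discharge would have to be by 3 December 2025 (31 December 2026 less 28 days, less 12 months), and recruitment would have to end earlier still. The cost is accrual: 28 days at 2.34 per day is about 65 patients, plus those lost to the allowance for stay, unless centres recruit faster.

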## Introduction

Emergency abdominal surgery is associated with increased rates of early and late postoperative complications, particularly the development of postoperative abdominal wall hernias [1]. This study protocol outlines the rationale and design of the PROPHECY trial, which will investigate this issue prospectively. Midline incisional hernias are among the most common complications after laparotomy and are associated with reduced quality of life, chronic pain, and need for complex reoperations [2, 3]. Despite a large number of analyzes on ways to reduce the incidence of this complication, it is still an important surgical problem [2]. Studies encompassing both elective and emergency procedures report postoperative hernia rates ranging from 2% to 40% [4]. This variation may be attributable to the often asymptomatic nature of certain hernias. An example are port-site hernias although generally perceived as rare, may occur more frequently than previously recognised, especially at umbilical sites [5]. Another significant surgical problem is parastomal hernias, occurring in up to 50% of patients with stomas [6]. The variability in reported incidence is also influenced by the method and duration of follow-up. True incidence rates are likely underreported, particularly in emergency surgery patients, where postoperative follow-up is frequently inconsistent or lacking.

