Numerous studies and guidelines have investigated factors influencing hernia formation. Patient-related risk factors include diabetes, obesity, chronic pulmonary disease, immunosuppression, and a history of abdominal surgeries [7]. The guidelines of the European Hernia Society emphasize the need for further research into methods of preventing the occurrence of postoperative hernias [2]. Procedure-related factors such as the type of incision, suture material, fascial closure technique, and use of surgical drains also play a role in hernia pathophysiology [1, 4, 8]. The World Society of Emergency Surgery (WSES) and European Hernia Society (EHS) guidelines recommend the “small bites” technique for fascial closure using slowly absorbable sutures, although most of the supporting evidence is derived from elective surgery [1, 9]. Despite these recommendations, high-quality prospective data focusing exclusively on emergency surgery settings are limited. These guidelines highlight the importance of conducting prospective studies to establish the efficacy of this technique in urgent and emergency surgical procedures [1].

Management of surgical wounds and abdominal wall closure in the emergency setting remains highly variable, with limited evidence guiding best practice. Surgical site infection—affecting approximately one-third of patients undergoing emergency procedures—is also a well-established risk factor for postoperative hernia development [2, 7] A less common but clinically significant complication, which also contributes to hernia formation, is wound dehiscence or evisceration [10]. Therefore, prevention of such early postoperative complications is crucial in reducing the risk of subsequent hernia formation. Furthermore, there is a lack of consensus regarding the effectiveness of postoperative interventions aimed at hernia prevention, such as the use of abdominal binders or recommendations concerning the timing of return to full physical activity [9].

Given the substantial clinical burden posed by postoperative hernias and the paucity of targeted data in emergency surgery, the PROPHECY trial aims to quantify hernia incidence and assess modifiable perioperative risk factors within this high-risk cohort.

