### Study Endpoints

#### Primary Endpoints

• Incidence of incisional hernia at the surgical site
• Incidence of port-site hernia following laparoscopy
• Incidence of parastomal hernia following stoma formation

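### Only patients suspected of hernia at the 12-month telephone interview are examined, so the primary endpoints estimate a lower bound on hernia incidence, not incidence itself

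*Protocol article*

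**What the plan says.** The Follow-Up Protocol section of the protocol article sets out a two-step pathway. First comes a single contact for everyone: "All participants will be followed up 12 months after discharge via telephone by a trained physician using a structured interview". Verification follows for a subset only: "In cases of suspected hernia, patients will be invited for outpatient clinical examination and ultrasound or CT imaging to confirm the diagnosis". The abstract summarises the same pathway: "Follow-up will be conducted via structured telephone interviews and clinical or imaging confirmation". Nothing in the article provides for examining or imaging patients whose interview raises no suspicion, for validating the interview, or for correcting for missed hernias.

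The primary endpoints carry no matching restriction. They read "Incidence of incisional hernia at the surgical site" and "Incidence of port-site hernia following laparoscopy", with a parallel entry for parastomal hernia. The Introduction says that the study "aims to quantify hernia incidence and assess modifiable perioperative risk factors within this high-risk cohort".

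The Introduction also discusses why published rates run from 2% to 40%. It offers this reason: "This variation may be attributable to the often asymptomatic nature of certain hernias". It adds that how, and for how long, patients are followed affects the reported figures. It then says: "True incidence rates are likely underreported, particularly in emergency surgery patients".

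**The concern.** The method of detection and the quantity claimed do not match. A telephone interview can find a hernia that the patient has noticed or already knows about. It cannot find one that the patient is unaware of, and the plan itself expects such hernias to exist. With no check on interview-negative patients, these hernias enter the primary proportions as non-cases.

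This affects the headline result. The study is sized to estimate each incidence to within 5 percentage points. That precision covers sampling error only. A confidence interval around a proportion that misses cases is centred too low, and recruiting more patients narrows it around the wrong value. If the result is reported as the incidence of hernia after emergency surgery, readers will take it as an estimate of a quantity that the design does not observe.

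**Working it through.** **Inputs from the article (Sample Size Justification):** 5-point precision at 95% confidence; 255 patients for incisional, 188 for port-site and 349 for parastomal hernia.

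**Inputs not in the article:** the anticipated incidences and the sensitivity *s* of the interview. Both are assumptions below.

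**Step 1. The plan's own figures.** No anticipated rate is given, so the sample sizes cannot be reproduced independently. They can be solved backwards through n = 1.96² p(1 − p) / 0.05²:
- 255 gives p ≈ 0.210. Check: 3.8416 × 0.21 × 0.79 / 0.0025 = 254.9, rounded up to 255.
- 188 gives p ≈ 0.143.
- 349 gives p ≈ 0.349.

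**Step 2. Effect of imperfect detection.** If confirmation removes false positives, observed incidence = s × true incidence, and the shortfall = (1 − s) × true incidence. With a true incisional rate of 21%:

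| Assumed s | Observed | Shortfall (points) |
|---|---|---|
| 0.5 | 10.5% | 10.5 |
| 0.6 | 12.6% | 8.4 |
| 0.7 | 14.7% | 6.3 |
| 0.8 | 16.8% | 4.2 |
| 0.9 | 18.9% | 2.1 |

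**Step 3. Sensitivity needed to keep the shortfall within 5 points.** Solve (1 − s) × p ≤ 0.05, so s ≥ 1 − 0.05/p:
- Incisional: 1 − 0.05/0.21 = 0.76
- Port-site: 1 − 0.05/0.143 = 0.65
- Parastomal: 1 − 0.05/0.349 = 0.86

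**Step 4. Does the confidence interval still cover 21%?** Use observed ± 1.96 √[o(1 − o)/n], where o is the observed proportion.
- n = 255, s = 0.6: 12.6 ± 4.1, or 8.5% to 16.7%. It excludes 21%.
- n = 255, s = 0.8: 16.8 ± 4.6, or 12.2% to 21.4%. It just includes 21%.
- n = 450 (500 less 10% dropout), s = 0.8: 13.3% to 20.3%. It excludes 21%. This treats the whole evaluable cohort as the incisional denominator, which the article does not state.

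**Step 5. Risk-factor comparisons.** If two groups have the same true risk but detection of 0.8 and 0.6 (both assumed), the observed risk ratio is 0.8/0.6 = 1.33. This shows only how sensitive the comparison is to unequal detection; the article gives no evidence that detection is unequal.

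**The case against.** The case for the plan is substantial, and several parts of it stand.

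- **The interview is better than self-report.** A trained physician puts structured questions to everyone. That may bring out a painless bulge, a hernia diagnosed in routine care, or a repair already done. So it would be wrong to say that only symptomatic hernias are counted, or that the data say nothing about incidence. A lower bound is useful.
- **The Introduction does not condemn this method.** Its remark on under-reporting points to emergency patients whose follow-up is inconsistent or absent, and contacting every participant at 12 months addresses that cause. The conflict rests on its two other remarks: that certain hernias are often asymptomatic, and that the follow-up method influences reported rates. The first is worded cautiously.
- **The size is assumed.** The 21% is an implied planning rate, not a documented true rate. If it came from clinically detected cases, applying a sensitivity loss to it counts the loss twice. At 90% sensitivity the shortfall is only 2.1 points.
- **Details may sit elsewhere.** How suspected patients who decline the visit are classified, and which sensitivity analyses are run, may be in a full protocol or SAP that is not shown. Their absence from the article is no fault.

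What remains is a mismatch between statements that the article does make: who is verified, what the endpoint is called, and what the study aims to measure. Telephone triage is a reasonable, openly disclosed choice on feasibility grounds, but it does not deliver unrestricted incidence.

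**Conclusion.** The point holds in this form: the three primary proportions are lower bounds on 12-month incidence, and the article presents them as incidence. The direction follows from the design, provided that confirmation admits few false positives. The size is not known. With an assumed true incisional rate of 21% and an assumed sensitivity of 50% to 90%, the shortfall is 10.5 to 2.1 points; it passes the planned 5-point precision only below a sensitivity of about 0.76.

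Three stronger readings are tempting, and the article does not support them:
- A reader might infer that the bias is bound to exceed 5 points. That depends on a sensitivity that is nowhere stated.
- A reader might infer that the results cannot be set against the published 2% to 40%, up to 30% and up to 50%. The detection methods behind those figures are not given, and some may resemble this one.
- A reader might infer that patients with surgical site infection are examined or imaged more often, which would inflate the link between infection and hernia. The article gives every participant the same 12-month contact and says nothing about extra imaging. Unequal detection is worth a scenario, not an assertion.

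**What to change.** - Define each of the three primary endpoints as a hernia suspected at the 12-month structured interview, including one already diagnosed or repaired, and confirmed by examination or imaging.
- State the aim and conclusions as a lower bound on 12-month incidence.
- Add a misclassification sensitivity analysis over an interview sensitivity of 50% to 90%, with one scenario in which detection differs between risk-factor groups.
- Report bounds that count suspected patients who do not attend for confirmation first as all cases, then as no cases.

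Hernias found incidentally on scans done for other reasons should not be added as cases unless the interview also raised them. Such a rule would contradict the definition above, and could itself create unequal detection if some groups are scanned more often.

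The cost is a narrower claim and a little more analysis. No extra visits or imaging are needed.

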### Study Endpoints

#### Primary Endpoints

• Incidence of incisional hernia at the surgical site
• Incidence of port-site hernia following laparoscopy
• Incidence of parastomal hernia following stoma formation

#### Secondary Endpoints

• Occurrence of surgical site infection (SSI)
• Occurrence of burst abdomen

### Statistical Analysis

The primary and secondary outcomes will be expressed as proportions with 95% confidence intervals. Continuous variables will be described using medians and interquartile ranges and analysed using Student’s t-test or the Wilcoxon test as appropriate. Categorical variables will be compared using the Chi-squared test. Univariate and multivariate logistic regression models will be applied to identify independent risk factors for postoperative hernia formation. Relative risk (RR) with 95% CI will be calculated. A p-value <0.05 will be considered statistically significant. All analyses will be conducted using R software in RStudio.

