### Sample Size Justification

To estimate a 5% precision for postoperative hernia incidence with 95% CI, a minimum of 255 cases is required. For port-site hernias, at least 188 patients are required; for parastomal hernias, 349. For secondary outcomes, the required sample sizes are 255 for SSI and 93 for burst abdomen. Sample size considerations are summarised in Table 1. To detect a moderate effect size (Cohen’s d = 0.3) with 80% power at α = 0.05, the required sample size is.
• Chi-squared test (1 df): 88 patients
• Chi-squared test (5 df): 143 patients
• Student’s t-test: 102 patients

**TABLE 1 T1:** Sample size rationale.

Endpoint	Sample size	Notes
Incisional Hernia	255	To estimate with 5% precision, 95% CI
Port-site Hernia	188	To estimate with 5% precision, 95% CI
Parastomal Hernia	349	To estimate with 5% precision, 95% CI
Surgical Site Infection (SSI)	255	To detect moderate effect size, 80% power
Burst Abdomen	93	To detect moderate effect size, 80% power

The total planned cohort will consist of 500 patients, which ensures sufficient power to assess primary and secondary outcomes while allowing for exploratory and subgroup analyses, including risk factors associated with specific surgical techniques or patient characteristics. This sample size also accommodates a potential dropout rate of up to 10% and supports the development of multivariate models with adequate statistical reliability.

To ensure feasibility across all participating centres, over-recruitment will be limited to a maximum of 50% above the calculated minimum sample size required for primary endpoints.

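### Naming Welch's t-test instead of Student's would protect the supporting comparisons of means if the groups differ in both size and spread

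*Protocol article*

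**What the plan says.** The Statistical Analysis section of the protocol article states: "Continuous variables will be described using medians and interquartile ranges". They are then to be "analysed using Student’s t-test or the Wilcoxon test as appropriate". The same section sets one threshold for all tests: "A p-value <0.05 will be considered statistically significant". It does not say which groups these two tests will compare.

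The Sample Size Justification section names the same test again. Under the statement "To detect a moderate effect size (Cohen’s d = 0.3) with 80% power at α = 0.05" it lists "Student’s t-test: 102 patients". So Student's test is named twice, and the Wilcoxon test is the only alternative offered. No standard deviation, or expected ratio of standard deviations, is given for any variable.

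Primary and secondary outcomes are to be reported as proportions with 95% confidence intervals. Independent risk factors for hernia are to be identified by logistic regression, and R is the named software.

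**The concern.** Student's two-sample test estimates one common variance. When the groups differ in size and also in spread, that estimate is dominated by the larger group, and the standard error of the difference is wrong. It is too small if the smaller group is the more variable (too many false positives) and too large if the smaller group is the less variable (real differences missed). Choosing the Wilcoxon test does not repair this, because its null distribution also assumes that the two groups have the same spread.

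A natural use of these tests in this study is to compare age, BMI or time to full activity between patients with and without a complication. The complication group would then be a minority. For hernia, logistic regression is planned alongside. For surgical site infection and burst abdomen the article names no regression model, so if continuous factors are compared for those outcomes, the t-test or Wilcoxon test is the only method stated. At stake is whether p < 0.05 means what it says in these supporting comparisons.

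**Working it through.** **Inputs from the article**

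- Cohort: "The total planned cohort will consist of 500 patients", with "a potential dropout rate of up to 10" per cent, so 500 × 0.9 = 450 evaluable.
- Hernia: the 255 patients for ±5% precision. From n = 1.96² p(1 − p)/0.05², p = 0.21 gives 3.8416 × 0.21 × 0.79/0.0025 = 254.9, which rounds up to 255. So the plan's own figure implies about 21%, or 0.21 × 450 ≈ 95 v 355. The Introduction gives a wider range: "postoperative hernia rates ranging from 2% to 40" per cent.
- Surgical site infection: about one-third (Introduction), or about 148 v 302.
- Burst abdomen: 4.4% as cited in the Discussion, or 0.044 × 450 ≈ 20 v 430.

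**Assumptions, not in the article**

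- Groups are formed by outcome.
- Data are normal with no true difference in means, and tests are two-sided at 0.05.
- The ratio r of the smaller group's SD to the larger group's SD runs from 0.67 to 1.5.

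**Formula**

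Let n₁ be the smaller group, with SD r, and n₂ the larger, with SD 1.

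- True variance of the difference: V = r²/n₁ + 1/n₂
- Pooled variance: s² = [(n₁ − 1)r² + (n₂ − 1)]/(n₁ + n₂ − 2)
- Variance the test uses: P = s²(1/n₁ + 1/n₂)
- Large-sample error rate: 2Φ(−1.96 √(P/V))

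**Worked case, 95 v 355, r = 1.5**

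- V = 2.25/95 + 1/355 = 0.02650
- s² = (94 × 2.25 + 354)/448 = 1.2623
- P = 1.2623 × 0.013343 = 0.01684
- √(P/V) = 0.797, so the effective cut-off is 1.96 × 0.797 = 1.563
- Error rate = 2Φ(−1.563) = 11.8%; simulation gives 12.0%

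**Error rate of Student's test at nominal 5% (large-sample formula; simulation agrees to within about 0.2 points)**

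| Split (N = 450) | r = 0.67 | 0.8 | 1 | 1.25 | 1.5 |
|---|---|---|---|---|---|
| 20 v 430 (4.4%) | 0.5% | 1.6% | 5.0% | 11.0% | 17.5% |
| 95 v 355 (21%) | 1.4% | 2.6% | 5.0% | 8.5% | 11.8% |
| 148 v 302 (33%) | 2.5% | 3.5% | 5.0% | 6.9% | 8.6% |
| 180 v 270 (40%) | 3.4% | 4.1% | 5.0% | 6.1% | 7.0% |
| 225 v 225 (50%) | 5.0% | 5.0% | 5.0% | 5.0% | 5.0% |

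In simulation Welch's test stays between 4.9% and 5.2% throughout. The Wilcoxon test at r = 1.5 rejects in 8.3% (95 v 355) and 10.0% (20 v 430) of datasets with equal means.

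**Power given up by Welch's test when the variances are equal (simulation, N = 500)**

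| Split | Effect d | Student | Welch |
|---|---|---|---|
| 105 v 395 | 0.3 | 77.7% | 77.4% |
| 50 v 450 | 0.3 | 51.9% | 50.8% |
| 22 v 478 | 0.5 | 62.7% | 59.2% |
| 10 v 490 | 0.5 | 34.4% | 29.0% |

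The stated 102 patients for Student's test does not follow from d = 0.3: a two-sided, two-sample test needs 176 per group, 352 in all. That is a separate matter, and nothing above depends on it.

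**The case against.** The strongest reply is that the article contains no error here. It names standard tests and qualifies them with a choice according to circumstances, and the variance form is a detail often settled in an analysis plan. Since t.test in R runs Welch's version by default, the recommended test might be run anyway. Part of this stands: the point is an improvement, not a demonstrated mistake. But the article does fix the test by name, and the stated choice is between two tests of which Welch's is not one. An analyst who follows the wording must switch the R default off, and one who keeps the default departs from the published text.

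The second reply is that the groups and SD ratios are supplied from outside. This stands in full. The section names no groups. Comparisons by surgical approach or technique are just as possible, with unknown splits. The 21% is back-calculated. The 4.4% comes from emergency laparotomy, while this cohort also includes appendicitis, cholecystitis and minimally invasive operations.

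A reader might infer three stronger things that the documents do not support:

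- **That the error rate is two to three times nominal.** Unequal sizes alone do no harm. At the hernia split, r = 1.25 gives 1.7 times nominal and r = 1.5 gives 2.4 times. More than three times appears in the table only for burst abdomen at r = 1.5.
- **That the study would report false hernia risk factors.** Those are to come from logistic regression, which this choice does not touch.
- **That Welch's test is free.** With very few events it costs some power, as shown above.

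**Conclusion.** The point holds as a minor, conditional improvement. Student's test loses its 5% error rate only where group sizes and SDs both differ. At the hernia split implied by the article the error would be about 8% to 12% for SD ratios of 1.25 to 1.5, and about 2.6% to 1.4% for ratios of 0.8 to 0.67. The distortion would be larger for burst abdomen, smaller at a one-third split, and absent with equal SDs or equal groups. The result rests on outcome-defined groups, normal data and assumed SD ratios. Only the group sizes can be traced to the article. The primary proportions and the hernia risk-factor models stand as they are.

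**What to change.** In the Statistical Analysis section, replace Student's t-test by Welch's unequal-variance t-test for every comparison of means. It would also help to say which groups are compared. No change of software is needed, because Welch's is the default of t.test in R.

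The edit is a change of name in one sentence. If the variances are in fact equal, the price is about 0.3 power points at the expected hernia split, about 1 point with 50 patients in the smaller group, and about 3 to 5 points (at d = 0.5) with only about 10 to 20. In that last range power is limited under either test.
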